### Blinding

All data will be collected by a non-managing investigator blind to treatment therapy. All analyzes will be performed blind to treatment therapy.

### Data Collection

Data will be collected and recorded on eCRF. All patient-related data are anonymously and numerically coded.

Data are as follows: age, sex, weight, SOFA score, SAPS II score, hospital and ICU admission reason, past medical history, comorbidities, VIS score, sedation drugs (type and infusion rate), hourly urinary output, amount of fluid, fluid balance, respiratory parameters (tidal volume, respiratory rate, positive end-expiratory pressure, inspiratory O_2_ fraction, plateau pressure), enteral nutrition (flow rate and kcal/kg/d), hemodynamic (heart rate, arterial blood pressure, pulse pressure), transthoracic echocardiographic evaluation, VA-ECMO parameters [flow rate, FmO_2_, O_2_ flow rate (l /min)].

All patients treated with VA-ECMO have daily transthoracic echocardiography until ECMO withdraw. Cardiac echocardiographic parameters are anonymously recorded at each time points and analyzed in a second time by an investigator non-involved in the patient's clinical management and blind to allocation treatment. Echocardiography is performed by an investigator with cardiac ultrasound certificate. Echocardiography parameters are: right and left cardiac chamber size, right and left systolic cardiac function, left and right diastolic parameters (mitral inflow, mitral annular velocities, tricuspid inflow, tricuspid annular velocities), cardiac output, inferior vena cava diameter, portal flow. The analysis will be performed offline in a simple blind manner.

### Assessment and Reporting of Adverse Events

Adverse events will be recorded in detail during both the follow-up periods. The reporting and documentation of adverse events will be classified as IMT-related or non-IMT-related. This safety analysis will be conducted at the end of our research.

### Statistics

#### Sample Size Calculation

Based on a LPS mean value of 110 ± 40 pmol/l (21), 34 patients should be randomized, 17 in each treatment arm will be necessary to demonstrate a decrease over 35% (16), with a bilateral alpha risk of 5% and a power of 80%. Assuming that 15% of patients would not be evaluable due to early death, we fixed the sample size to 40 patients, 20 patients in each treatment arm.

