	**Exclusion criteria**
	• ≤ 24 h of duration of Oxiris or RRT treatment

*ECMO, Extracorporeal membrane oxygenation; RRT, renal replacement therapy; h, hours*.

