#### Data-Analysis Plan

The data will be analyzed in intention-to-treat and per-protocol. The variables will be presented as mean ± SD, or as median [25–75% IQR], as appropriate. The treatment groups will be presented comparatively after the randomization. The qualitative variables will be compared using the Chi-square test or Fisher's exact test. The quantitative variables will be compared using the Student's test or a non-parametric test, as appropriate. Longitudinal data will be processed using mixed-models. The normality will be checked graphically, with histograms and QQ plots and using the Shapiro-Wilk normality test.

The evaluation of the primary endpoint will be considered as a comparison of means. The statistical analysis will be performed using R Studio software. A *p* < 0.05 will be considered statistically significant.

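### At 17 evaluable patients per arm the planned t-test has about 78% power, not 80%, and the 15% loss allowance is narrower than the plan's own 24 h exclusion

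*Protocol article*

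**What the plan says.** In the protocol article, the Sample Size Calculation section starts from an LPS mean of 110 with SD 40 pmol/l and a decrease of more than 35%. It concludes that "34 patients should be randomized, 17 in each treatment arm", "with a bilateral alpha risk of 5% and a power of 80" percent. It then assumes that 15% of patients "would not be evaluable due to early death" and fixes the total at 40, that is 20 per arm. No formula is named.

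The Data-Analysis Plan treats the primary endpoint as a comparison of means. Quantitative variables are compared by Student's "test or a non-parametric test, as appropriate". Both intention-to-treat and per-protocol analyses are announced.

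Table 2 lists one exclusion criterion, separate from the non-inclusion criteria: 24 h or less "of duration of Oxiris or RRT treatment". It gives no reason for stopping and no analysis set to which the criterion applies.

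**The concern.** With fewer than 20 patients per arm, a sample size from the normal formula is slightly too small for a t-test, because the t-test also pays for estimating the SD. The stated 80% may therefore not be the power of the planned analysis. The three extra patients per arm offer no cushion if the plan expects to lose them.

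The second issue is the kind of loss. The allowance names early death. The exclusion in Table 2 depends on how long the filter ran, which is known only after randomisation, and it applies whatever ended the treatment. A living patient whose filter treatment ends by 24 h would be removed without having been budgeted for. Removing randomised patients for a post-randomisation event is also hard to square with an intention-to-treat analysis.

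At stake is how a non-significant result would be read, and whether the primary comparison keeps the groups as randomised.

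**Working it through.** **Inputs.** From Sample Size Calculation: mean 110, SD 40, decrease 35%, two-sided 5%, power 80%, 17 per arm, 15% non-evaluable, 40 randomised. From Randomization: 1:1 allocation. Assumption: SD 40 also in the treated arm, because the article gives only one SD.

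Difference = 0.35 × 110 = 38.5 pmol/l. Standardised difference d = 38.5/40 = 0.9625.

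**1. The plan's figure reproduces.** Normal formula: n = 2 × (1.960 + 0.842)² / 0.9625² = 16.94, so 17 per arm. Power at 17: Φ(0.9625 × √(17/2) − 1.960) = Φ(2.806 − 1.960) = 80.1%. Inflation: 34/0.85 = 40.

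**2. Power of the t-test.** Non-centrality = 0.9625 × √(n/2), with 2n − 2 degrees of freedom. At n = 17 this is 2.806 on 32 degrees of freedom, against a critical value of 2.037.

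| Evaluable per arm | t-test power |
|---|---|
| 15 | 72.1% |
| 16 | 75.0% |
| 17 | 77.7% |
| 18 | 80.1% |
| 20 | 84.3% |

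The exact n for 80% is 17.96, so 18 per arm. A simulation of 100,000 trials at 17 per arm also gave 77.7%. At 17 per arm, 80% power is reached at d = 0.991, that is 0.991 × 40 = 39.6 pmol/l, or 39.6/110 = 36.0%.

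**3. Does enrolling 20 per arm close the gap?** Only if nobody is lost. The plan expects 40 × 0.85 = 34 evaluable, which is 17 per arm. If each patient is lost at random with probability 15%, average power is 77.3%, and the chance that both arms keep at least 17 is 42%.

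**4. Losses other than death.** The article gives no rate for them, so the following total loss rates are assumptions that show the sensitivity only. Average t-test power from 20 per arm is 74.5% at 20% loss, 71.4% at 25% and 68.1% at 30%.

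**5. What baseline adjustment could recover.** Adjusting for the baseline (H0) LPS multiplies the residual SD by √(1 − r²), where r is the baseline-to-24 h correlation. Requiring 0.9625/√(1 − r²) ≥ 0.991 gives r ≥ 0.24, or about 0.25 once the lost degree of freedom is counted. Chance baseline imbalance inflates the variance by about 1 + 1/30 at 17 per arm. The condition is then 1 − r² ≤ (0.9625/0.991)²/1.033 = 0.913, so r is about 0.3. The article gives no value for r.

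**The case against.** The best defence is that the stated figure is not an arithmetic error. The usual normal formula gives 17 per arm, the article names no other, and the inflation is exact. The gap is one patient per arm and 2.3 points of power, which is less than the uncertainty in the inputs: t-test power at 17 per arm is 79.7% with SD 39 and 81.7% with SD 38. If the treated SD fell in proportion to the mean (40 × 0.65 = 26), power would be about 90%. All of this stands, and it makes the power point minor. It does not make 80% the power of the t-test under the one SD that the article states.

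On losses, the defence is that early death may be the main reason for 24 h or less of treatment, so 15% may already cover most exclusions. The announced intention-to-treat analysis may also mean that the exclusion was meant for the per-protocol set. Either is possible, but the article says neither.

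Three stronger readings are tempting and not supported:

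- A reader might infer that the rank test has only 75% power. That figure comes from normal data with equal SDs, where the plan would not turn to a rank test. With skewed (lognormal) data and the plan's means at 17 per arm, simulated rank-test power was about 87% with SD 40 in both arms and about 92% with SD 26 in the treated arm.
- A reader might put the risk of missing the planned effect as high as 29%. That needs about 25% loss, which the article does not state.
- A reader might call the lack of slack in the 15% allowance a defect. Exact inflation is correct practice.

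**Conclusion.** The point holds as a minor correction to the stated power and a more substantive mismatch over who is analysed.

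Power: with Student's test and SD 40 in both arms, the planned 17 evaluable patients per arm give about 78%. The stated 80% corresponds to 18 per arm or to a 36% decrease. The size of the trial need not change on this account.

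Analysed patients: the loss allowance counts early death, while Table 2 removes anyone treated for 24 h or less. Every such removal of a living patient takes the trial below its budgeted number, and it conflicts with intention-to-treat unless confined to the per-protocol set. How much power this would cost cannot be stated, because no rate of non-death stops is given.

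**What to change.** Keep 40 patients and make three changes.

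1. **Restate the power.** For example: 34 evaluable patients (17 per arm) give about 78% power by two-sided t-test at 5% for a 38.5 pmol/l (35%) difference, assuming SD 40 in both arms; 80% power applies to 39.6 pmol/l (36%).
2. **Align exclusion, loss allowance and analysis set.** Take the 24 h LPS sample in every living randomised patient, whatever the filter run time, and analyse it as randomised. The arterial draw listed under Endpoints or Outcome Measures does not need a running filter. Use the 24 h treatment criterion to define the per-protocol set only. Losses to the primary analysis are then essentially the early deaths that the 15% was meant to cover.
3. **Adjust the primary comparison for H0 LPS**, specified in advance. Study samples are already scheduled before membrane placement. This brings power to 80% or more if the baseline-to-24 h correlation is about 0.25 or higher, or about 0.3 if chance baseline imbalance is counted. The correlation is an assumption and should be labelled as one.

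The cost is a few sentences of text and a slightly lower stated power. No patients or scheduled time points are added. The alternative, restoring 80% for the unadjusted t-test, would need 36/0.85 = 42.4, so 43 patients, or 44 in equal arms.

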#### Data-Analysis Plan

The data will be analyzed in intention-to-treat and per-protocol. The variables will be presented as mean ± SD, or as median [25–75% IQR], as appropriate. The treatment groups will be presented comparatively after the randomization. The qualitative variables will be compared using the Chi-square test or Fisher's exact test. The quantitative variables will be compared using the Student's test or a non-parametric test, as appropriate. Longitudinal data will be processed using mixed-models. The normality will be checked graphically, with histograms and QQ plots and using the Shapiro-Wilk normality test.

The evaluation of the primary endpoint will be considered as a comparison of means. The statistical analysis will be performed using R Studio software. A *p* < 0.05 will be considered statistically significant.

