### Randomization

The 1:1 ratio randomization is performed by the investigator after the patient's enrollment, using a dedicated e-platform made with CleanWeb TM. This process is controlled by individual usernames and newly created passwords for each enrollment. A second checkup for the inclusion, non-inclusion and exclusion criteria is done at this point. Technical support is provided by the Research Methodology Support Unit from our university-affiliated hospital, which also keeps a record of the full randomization process.

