### Endpoints or Outcome Measures

The primary endpoint is the LPS serum level after 24 h of continuous RRT with Oxiris membrane.

The secondary endpoints are: (1) the VIS score [defined using the formula: Dopamine infusion rate (mcg/kg/min) + Dobutamine infusion rate (mcg/kg/min) + 100 x Epinephrine infusion rate (mcg/kg/min) + 10 x Milrinone infusion rate (mcg/kg/min) + 10,000 x Vasopressin infusion rate (units/kg/min) + 100 x Norepinephrine infusion rate (mcg/kg/min)]; (2) the SOFA score at day 1, 2, 3 and 7; (3) Serum levels kinetic of cytokines (IL1, IL6, IL 4, IL10, TNF-alpha, interferon gamma, MCP1), CRP, procalcitonin, I-FABP, GLP-1, zonuline, citrulline from RRT initiation, to 6 h after initiation, day 1, day 2, and day 3 of treatment; (4) LPS plasma concentration, (5), ICU length of stay and 30-day mortality. Patients' follow-up is 30 days after initiation of VA-ECMO.

Serial standard usual blood analysis set is drawn at several time points: at the enrollment moment (before RRT membrane placement), after 6, 24, 48, and 72 h of continuous RRT. The study-specific blood analyses are performed at the same time moments. The reference time (T0) is the start of RRT for all group (control and intervention).

At each time point, one EDTA tube of 5 ml is taken via the arterial catheter, and 2 sets of EDTA tubes of 5 ml and are taken on the RRT circuit (one before and one after the filter membrane).

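### The primary comparison of 24 h LPS means names no baseline covariate although a pre-membrane sample is scheduled, which gives up precision, and it is unclear whether a rank test may replace it

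*Protocol article*

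**What the plan says.** All references are to the protocol article.

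- **Endpoint** (Endpoints or Outcome Measures): the LPS serum level after 24 h of continuous RRT, at a single time point.
- **Primary analysis** (Data-Analysis Plan): "The evaluation of the primary endpoint will be considered as a comparison of means". No covariate is named. Mixed models are reserved for longitudinal data and are not linked to the 24 h endpoint.
- **Sampling** (Endpoints or Outcome Measures): standard blood is drawn "at the enrollment moment (before RRT membrane placement), after 6, 24, 48, and 72 h of continuous RRT", and the study-specific assays follow the same schedule. Table 1 (Study Design) marks the study analysis set at H0.
- **General rule for quantitative variables** (Data-Analysis Plan): Student's test "or a non-parametric test, as appropriate". Normality is examined with histograms, QQ plots and the Shapiro-Wilk test.
- **Sample size** (Sample Size Calculation): "Based on a LPS mean value of 110 ± 40 pmol/l (21), 34 patients should be randomized", for a 35% decrease, "with a bilateral alpha risk of 5% and a power of 80"%. The total is raised to 40 for 15% non-evaluable patients.

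**The concern.** Two features of the primary analysis deserve a second look.

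First, a pre-treatment value of the outcome itself is normally the most useful covariate in a small trial. Here it appears to be collected, but the stated primary comparison does not use it. With about 17 evaluable patients per arm, the width of the confidence interval largely decides whether the trial can answer its question.

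Second, the plan describes the primary evaluation as a comparison of means, and in the same section allows a non-parametric test for quantitative variables after normality checks. A rank test does not compare means. If the general rule reaches the primary endpoint, the test and the quantity it estimates are settled only once the data are seen.

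**Working it through.** **Inputs from the documents.** Mean 110 and SD 40 pmol/l, a decrease of 35%, two-sided alpha 5%, power 80% and 15% non-evaluable (Sample Size Calculation); 1:1 allocation (Randomization).

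**Assumed input.** The correlation ρ between H0 and 24 h LPS is not given, so a range is shown.

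**1. The plan's own figure.** The difference is 0.35 × 110 = 38.5 pmol/l, and the standardised effect is 38.5/40 = 0.9625.

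n per arm = 2 × [40 × (1.960 + 0.842)/38.5]² = 16.94, so 17 per arm and 34 in total. Then 34/0.85 = 40. Both figures reproduce. They use the raw SD, as an unadjusted two-sample comparison requires.

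Power at 17 per arm is 80.1% by the normal approximation and 77.7% by the noncentral t distribution. If all 20 per arm are evaluable, the t-based figure is 84.3%.

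**2. Effect of baseline adjustment at 17 per arm.** The residual SD is 40 × √(1 − ρ²), and the standard error of the difference is that SD × √(2/17). Power uses the noncentral t with 32 df unadjusted and 31 df adjusted.

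| ρ (assumed) | SE, pmol/l | 95% CI half-width, pmol/l | Power |
|---|---|---|---|
| unadjusted | 13.7 | 27.9 | 78% |
| 0.2 | 13.4 | 27.4 | 79% |
| 0.3 | 13.1 | 26.7 | 81% |
| 0.5 | 11.9 | 24.2 | 88% |
| 0.7 | 9.8 | 20.0 | 97% |

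At ρ = 0.5 the interval narrows by 1 − 24.2/27.9 = 13%. A simulation of 8,000 trials with normal data and ρ = 0.5 gave 87.7% power adjusted and 78.2% unadjusted, which agrees with the formula.

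**3. Chance baseline imbalance.** If the baseline SD is also 40 (an assumption), the SD of the chance difference between arms at H0 is 40 × √(2/17) = 13.7 pmol/l. With equal SDs, only ρ times this reaches the 24 h contrast: 4.1, 6.9 or 9.6 pmol/l at ρ = 0.3, 0.5 or 0.7. Divided by 38.5, that is about 11%, 18% or 25% of the planned effect.

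**4. If normality checks choose the test.** Simulated rule: t-test if neither arm fails Shapiro-Wilk at 5%, otherwise Mann-Whitney; 17 per arm, 8,000 trials per scenario.

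| Assumed distribution (mean 110, SD 40) | At least one arm fails | Type I error of the two-stage rule |
|---|---|---|
| Normal | about 10% | 5.1% |
| Log-normal | about 45% | 5.7% |

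**The case against.** The strongest reply is that nothing here is an error. The unadjusted comparison of randomised arms is unbiased, the sample size is right for it, and a condensed article may leave covariates to a fuller plan. A baseline-adjusted contrast is itself a comparison of means. Most of this stands, and it limits the point to efficiency and clarity. It does not remove the point, because the article goes as far as stating the primary analysis, names no covariate, and sizes the trial on the raw SD.

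The documents do not support several stronger readings that a reader might infer:

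- *That the primary test will be chosen from the data.* The primary endpoint has its own sentence, after the general rule, which points to a comparison of means. No text exempts it from the general rule, so this is an ambiguity. Shapiro-Wilk is also listed beside graphical checks and is not described as an automatic selector.
- *That the choice of test is close to a coin flip.* This needs log-normal LPS, which the documents do not state. With normal data the figure is about 10%. In neither case is type I error seriously inflated.
- *That a chance baseline imbalance of 13.7 pmol/l, 36% of the effect (13.7/38.5), carries over in full.* That would require ρ = 1. What does carry over is already reflected in the standard error and is not an added bias.
- *That planning a percentage fall conflicts with analysing a difference.* The 35% enters the calculation as 38.5 pmol/l, and that absolute difference reproduces the 17 per arm. Planning and analysis are on the same scale.

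**Conclusion.** The point holds as a worthwhile improvement to a valid analysis. The stated primary comparison leaves out a baseline measurement that the schedule already provides. The gain in power from using it ranges from about 1 percentage point at ρ = 0.2 to about 19 points at ρ = 0.7 (78% to 97%), with 10 points at ρ = 0.5. The gain cannot be stated more closely without ρ.

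That baseline LPS is measured in every patient is inferred from three places: the sampling schedule with Table 1, the LPS kinetics objective, and the abstract's LPS monitoring over 72 h. The figures use the expected 34 evaluable patients, not the 40 randomised.

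The role of the non-parametric option is a separate and smaller ambiguity. Its cost is an unfixed test and estimand.

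**What to change.** Before unblinding, pre-specify one primary model: ANCOVA of 24 h LPS on treatment and H0 LPS, or the baseline-adjusted 24 h contrast from the mixed model already planned for longitudinal data. Fix the scale at the same time. The log scale is a reasonable option and would give a geometric mean ratio with its 95% confidence interval. State that normality checks do not select the primary test, and keep the rank test as a sensitivity analysis.

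The cost is one degree of freedom and a few sentences in the plan. No extra samples, visits or patients are needed, and the sample size can stay as it is.

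The timing matters because a covariate or test chosen after the results are known would be open to challenge.

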## Discussion

The results of this study will bring insights into the potential use of the Oxiris membrane in managing cardiogenic shock supported by VA-ECMO. Furthermore, the particular focus on the LPS serum levels profile will provide a better understanding of the mechanisms of therapeutical benefit of Oxiris membrane.

Blood purifications is a subject of rising interest, and some authors proposed a rationale for blood purifiers use to control VA-ECMO-induced systemic inflammation (22). However, the use of cytokine absorbent filters is still controversial and lacking scientific evidence. The Cytosorb membrane (Cytosorbents, NJ, USA) has been studied in various settings (23–26). The Cytosorb membrane is able to eliminate a large diversity of cytokines, but also other plasmatic molecules like DAMP, PAMP, complement factors (27–29). However, Cytosorb did not improve clinical outcomes when used during the cardio-pulmonary bypass (30). Moreover, in patients suffering of SARS-Cov2 supported by ECMO, Cytosorb was unable to decrease interleukin 6 concentrations, and was associated with higher mortality (31). These findings suggest that inflammation is insufficiently controlled by the Cystosorb membrane and one hypothesis is that an alternative pathway might be involved.

The Oxiris membrane (Baxter Investment Co., Ltd., Shanghai, China) is another adsorbing membrane that has been less studied. One important difference between those 2 membranes is that the Oxiris membrane is able to remove both interleukins and LPS (16, 28). Those properties seem to promote hemodynamic stabilization and even organs failure improvement during states of sepsis-related circulatory failure (17, 32–35). Because LPS might play a pivotal role in enhancing inflammation during the ischemia-reperfusion phase, the additional LPS removal properties of the Oxiris membrane by reducing the triggering of the TLR-4 pathway could provide a clinical benefit. As this clinical benefit has not yet been demonstrated in our population those hypotheses remain speculative and randomized trials are needed to provide robust answers.

Indeed, the literature on the subject is parse and mainly performed in human neonates or animals with immature gastrointestinal tract and/or different immune system (7, 11). No study has evaluated the effect of retrograde VA-ECMO flow on intestinal perfusion and intestinal barrier. Despite cardiogenic shock is associated with intestinal translocation and high level of LPS, few studies have demonstrated this point in cardiogenic shock supported with VA-ECMO. In addition, our study doesn't include a control group of cardiogenic shock patients without VA-ECMO support. All these points could be a limit of the study. Nevertheless, by focusing on LPS removal kinetic our study will allow clarifying for the first time whether the Oxiris device lowers the LPS burden in refractory cardiogenic shock supported by ECMO (10–12).

One aspect of particular interest in our population is the predictability of the timing of the injury that allows early treatment before the irreversible consequences of ischemia-reperfusion. This fact represents an advantage comparing to medical conditions-induced cytokine storm. Nevertheless, the right initiation timing during VA-ECMO is debatable and to be determined (22). One should also consider the more extensive ICU discussion about the adequate RRT initiation moment (29). We chose to enroll the patients no later than 12 h after VA-ECMO implantation in order to anticipate the irreversibility of ischemia-reperfusion injury.

The adding of an extracorporeal circuit seems to be clinically tolerated, but it is difficult to propose it for patients who do not need RRT. Because Oxiris membrane is used on VA-ECMO, RRT blood flow rate may be low and the LPS clearance rate may be insufficient. Broman et al. demonstrated that RRT with a mean blood flow rate of 132 ± 69 ml min^−1^ is able to significantly decrease endotoxin level (17). This blood flow rate is below the blood flow rate in our study. The main concern is the risk of hemorrhage due to vascular access, extracorporeal-induced coagulopathy, and the immune reactions to the heparin-coated circuit. Regarding this concern, the patients on VA-ECMO are already at risk with a larger extracorporeal circuit, large cannulae for vascular access and already on heparin anticoagulation. The addition of the RRT circuit can be performed on the VA-ECMO circuit, as already shown (36).

In conclusion, the study results will be of significant importance in the management of refractory cardiogenic shock support by VA-ECMO, and will bring pathophysiological insights about the intestinal barrier and LPS role in this context.

